## Background

More than 1/3^rd^ of adults are overweight or obese [1] which contributes to major causes of preventable death including cardiometabolic diseases (cardiovascular disease, type 2 diabetes) as well as some cancers. There is increasing evidence that both short sleep duration and circadian rhythm misalignment adversely impact cardiometabolic health [2]. A meta-analysis demonstrated short sleep duration was associated with a 37% higher risk for diabetes mellitus, 16% higher risk for cardiovascular disease and 38% higher risk for obesity [3]. In addition, circadian misalignment, defined as mistimed sleep in relation to internal circadian rhythm, is also an independent predictor of cardiometabolic health [4, 5]. When exposures to short sleep duration and circadian misalignment are combined in laboratory experiments, research has demonstrated these exposures have an additive effect [6, 7]. However, little is known about how chronic exposure to sleep loss and circadian misalignment in daily life affect cardiometabolic health.

Our laboratory has focused on the translation of laboratory research to real-world settings and studying the effects of common types of circadian misalignment in daily life. In our previous study, we examined the role of circadian timing and alignment (sleep timing in relation to the circadian phase marker of dim light melatonin onset) on obesity and cardiometabolic risk factors in a sample of healthy young to middle aged adults with habitual sleep duration of at least 6.5 h [8]. We discovered that circadian misalignment, rather than timing per se, was associated with greater caloric and carbohydrate intake, consuming a greater number of meals, and in overweight participants, insulin resistance [8, 9].

A limitation of our study design was that by excluding individuals with short sleep duration, we could not examine the role of sleep duration in this study. Given that more than half of potential participants were ineligible for our study due to short sleep duration (particularly those with later sleep times), this demonstrates how the interaction between sleep duration and circadian alignment may be particularly important to understanding risk in daily life. In addition, results of our study also suggest that neurobehavioral determinants of increased hedonic eating (e.g., impulsivity) may play a role in the cardiometabolic consequences of short sleep duration and circadian misalignment.

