## Methods/Design

### Participants and eligibility criteria

Participants will include adults aged 18–55 years with BMI ranging from 25.0–34.9 kg/m^2^who have habitual sleep onset times between 10:30 pm and 3:00 am, verified by 7 days of wrist actigraphy. Exclusionary criteria include: 1) High risk or presence of sleep disorders as assessed by the questionnaires and overnight OSA screening; 2) Diabetes diagnosis or HbA1c (glycated hemoglobin) > 7.0%; 3) History of cognitive or neurological disorders; 4) Presence of major psychiatric disorders, current alcohol or substance abuse as determined by screening questionnaires; 5) Unstable or serious medical illness; 6) Overnight shift work or travel over 2 or more time zones in the past 2 months; 7) Use of hypnotic, stimulant or medications known to affect melatonin concentrations such as beta blockers, daily NSAIDs or antidepressants; 8) Current smoking, 9) Daily caffeine intake > 300 mg, 10) Pregnant or lactating.

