#### Wrist actigraphy protocol

Participants will wear the Actiwatch Spectrum (Philips/Respironics, Bend, OR) on the nondominant wrist for 7 days at screening/baseline, prior to the phase assessment, at 6 and 12 months. Actiwatches will be set with 30-s epoch length and medium sensitivity. Actigraphic sleep parameters will be calculated using Actiware-Sleep 6.1.1 software (or the current version) with default settings and included the following variables: sleep onset time, sleep offset time, and sleep duration. Actigraphy files will be scored using a standardized protocol using inputs of marker use, light and activity [16].

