#### Circadian measures

Saliva samples will be collected every 30 min in the 7 h prior to habitual sleep onset time, as determined by actigraphy at screening. DLMO time will be calculated for each profile, and defined as clock time when salivary melatonin concentrations rise above the average of three low daytime values plus twice the standard deviation of the baseline values [17]. Circadian alignment will be calculated as duration between DLMO and average sleep onset time in adjacent week, consistent with our prior study [8].

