### Data analysis

Data will be analyzed using R (Version 3.2)^61^ All analyses will be performed on an intent-to-treat basis. Significance will be defined p values < 0.05 on two tailed tests.

#### Aim 1

Cross-sectional relationships between circadian alignment, sleep duration and cardiometabolic health.

We will use a multivariable linear regression to model the relationship between insulin sensitivity index at baseline (the outcome) with the baseline circadian alignment, controlling for sex, age, and race/ethnicity. Secondary analyses will be conducted similarly using other measurements at baseline. Other variables, all taken at baseline, being modeled will include metabolic variables – acute glucose response, disposition index, HbA1c, BMI, and body fat – neurobehavioral variables – delay discounting and stop/signal – and behavioral variables – diet quality and physical activity.

In all models, transformation of the outcome will be done if needed for normality. Regression diagnostics will be examined to check for outliers or influential data points as well as for nonlinear relationships with circadian alignment. Additional exploratory analyses will add pairwise interaction terms to evaluate effect modification by sleep duration and sex.

#### Aim 2

We will examine the differences in morning and evening measurements in several outcomes. The primary outcome we will be examining is the calories consumed. Secondary outcomes will be neurobehavioral variables – delay discounting, stop/signal, and processing speed – and mood or hunger rating variables – sleepiness, hunger, and appetite. First, we will use paired t-tests to examine differences for all outcomes. We will then use multivariable linear regression to model the relationship between the difference (morning vs. evening) in calories consumed and DLMO time, controlling for sex, age, and race/ethnicity. Regression diagnostics will be examined for nonlinearity, outliers, and influential data points. For additional outcomes, we will examine similar models.

#### Aim 3

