We will examine longitudinal changes in several outcomes over the course of a year, specifically at three time points – baseline, 6 months, and 12 months – and how they related to circadian alignment at baseline. We will first look at the relationship between our primary outcome, HbA1c, and circadian alignment (at baseline), while adjusting for covariates age at baseline, sex, race/ethnicity and sleep duration. Visit time (baseline, 6 months, and 12 months) will be modeled as a categorical factor and an interaction between visit time and our main predictor, baseline circadian alignment, as well as each of the covariates. We will use a linear mixed effects regression model with an unstructured covariance model to account for serial correlation. If convergence fails, we will compare alternative models for serial correlation, such as heteroscedastic auto-regressive models and compound symmetry, using likelihood tests or AICs to choose the preferred model. A similar procedure will be followed for additional outcomes BMI, body fat, diet and physical activity.

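### Aim 3 models alignment as the difference between sleep onset and DLMO but includes neither time as a term, so an effect of late sleep or late circadian phase alone could be read as an alignment effect

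*Protocol article*

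**What the plan says.** Under Circadian measures, the exposure is defined as a difference: "Circadian alignment will be calculated as duration between DLMO and average sleep onset time in adjacent week".

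Under Data analysis, Aim 3, the HbA1c model is a mixed model on baseline, 6 and 12 months with baseline alignment as main predictor, "while adjusting for covariates age at baseline, sex, race/ethnicity and sleep duration". It has "an interaction between visit time and our main predictor, baseline circadian alignment, as well as each of the covariates". The other outcomes get the same treatment: "A similar procedure will be followed for additional outcomes BMI, body fat, diet and physical activity".

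Neither sleep onset time nor DLMO time is an Aim 3 term. DLMO time is a predictor only in Aim 2, which models the "difference (morning vs. evening) in calories consumed and DLMO time, controlling for sex, age, and race/ethnicity". Both components are available: Wrist actigraphy protocol lists "sleep onset time, sleep offset time, and sleep duration", and DLMO is computed for each melatonin profile.

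The Background draws the distinction at issue when it reports the group's previous study: "We discovered that circadian misalignment, rather than timing per se, was associated with greater caloric and carbohydrate intake".

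**The concern.** Entering only the difference forces onset and DLMO to have equal and opposite effects, and no planned analysis tests that constraint. Alignment is generally correlated with at least one of its components. If HbA1c, BMI or body fat changes with late sleep onset alone, or with late DLMO alone, the alignment-by-visit slope can be non-zero although the interval itself plays no part. Sleep duration is in the model, but it measures how long people sleep and not when.

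At stake is interpretation. The Discussion expects to say whether alignment affects 12-month cardiometabolic change, and the group's previous finding turned on alignment as distinct from timing. The Aim 3 model as listed cannot tell the two apart.

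**Working it through.** **The plan's own figures.** Sample size justification gives minimum detectable slopes for Aim 1 (none for Aim 3). They reproduce: (1.960 + 0.842) × 32.1 / (57 × √96) = 0.161, and 0.161 / √(1 − 0.4²) = 0.176. They are not in dispute. From them I take alignment SD = 57 min and n = 96.

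**Assumed, not in the documents.** Onset SD 60–70 min; DLMO SD 60–75 min; correlation of sleep duration with onset 0 or −0.4; correlation of the acting component with the outcome 0.4 or 0.2. For orientation, eligibility requires "habitual sleep onset times between 10:30 pm and 3:00 am", a 270-min window; a uniform spread over it would give SD 270/√12 = 78 min.

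**Algebra.** Write A = S − D, with S onset and D DLMO. Then Cov(S,D) = [Var(S) + Var(D) − 57²]/2. With A alone in the model:

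- only S acts, slope 1: coefficient of A = [Var(S) − Cov(S,D)] / 57²
- only D acts, slope 1: coefficient of A = [Cov(S,D) − Var(D)] / 57²

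The two differ by Var(S − D)/57² = 1 whatever the SDs, so at least one pure timing effect passes into the alignment coefficient at half its size or more.

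| SD(S) | SD(D) | Cov(S,D) | S only | D only | corr(A,S) | corr(A,D) |
|---|---|---|---|---|---|---|
| 60 | 60 | 1975.5 | +0.50 | −0.50 | 0.47 | −0.47 |
| 60 | 75 | 2988.0 | +0.19 | −0.81 | 0.18 | −0.62 |
| 70 | 60 | 2625.5 | +0.70 | −0.30 | 0.57 | −0.28 |
| 70 | 75 | 3638.0 | +0.39 | −0.61 | 0.32 | −0.46 |

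A DLMO-only effect has the opposite sign: later DLMO shortens the interval, so it would read as an effect of a short interval. One of the two fractions can be near zero (SD 45 and 75 give −0.05 for onset only), but then the other is large (−1.05).

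Adjusting for sleep duration changes little. With SDs 60 and 60 and a duration–onset correlation of −0.3 to −0.5, the onset-only fraction goes from 0.50 to 0.46–0.40 and the DLMO-only fraction from −0.50 to between −0.54 and −0.60.

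**How often alignment would reach p < 0.05.** Take a single change score, with alignment, sleep duration and four unrelated covariates: 7 parameters, 89 residual df. With duration unrelated to onset, ρ = r × corr(A, component), λ = ρ√89/√(1 − ρ²), and the rate is about Φ(λ − 1.99) plus a small opposite tail. At r = 0.4:

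- SDs 70/60, onset only: ρ = 0.4 × 0.570 = 0.228, λ = 2.21, rate 59%
- SDs 60/75, onset only: ρ = 0.072, λ = 0.68, rate 10%
- SDs 60/75, DLMO only: ρ = −0.247, |λ| = 2.40, rate 66%
- SDs 70/60, DLMO only: ρ = −0.114, |λ| = 1.08, rate 18%

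Simulation over all four SD pairs and both duration–onset correlations gives about 8–59% (onset only) and 16–70% (DLMO only) at r = 0.4, and about 6–19% and 9–24% at r = 0.2. Repeat simulations move the ends by a few points; the lower DLMO-only end falls between 16% and 20%. The nominal rate is 5%.

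**What a second term does.** Since b_S·S + b_D·D = b_S·A + (b_S + b_D)·D, adding DLMO to alignment is the same model as entering onset and DLMO. The DLMO coefficient becomes b_S + b_D, which is zero when effects are equal and opposite. The alignment coefficient becomes b_S, the onset effect given DLMO: 0 if only DLMO acts, but 1 if only onset acts. One coefficient is therefore not enough. A, S and D together have rank 2, so all three cannot be entered.

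The DLMO term reaches p < 0.05 in about 84–97% of studies at r = 0.4, but only about 30–48% at r = 0.2. It does so in about 5% when alignment is the true driver.

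**Precision.** With duration unrelated to onset, the alignment standard error grows by 1/√(1 − corr(A,D)²): 1.04 at SDs 70/60 and 1.27 at 60/75. With the duration–onset correlation at −0.4, the range over the grid is about 4–35%. Under wider SDs (onset 45–78, DLMO 60–90 min) the factor runs from 1.01 to 2.40.

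**The case against.** The case for leaving the plan alone has four parts.

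- Alignment is the pre-specified exposure, and its coefficient estimates the association the authors set out to estimate. This stands, and is why the primary model should stay.
- The contrast with timing describes a previous study; it is not a stated Aim 3 hypothesis. A reader might infer that the protocol commits itself to concluding that misalignment and not lateness drives 12-month change. It does not: the aims and Discussion speak of whether sleep and circadian alignment predict or affect change. But the Background shows that the authors consider the distinction meaningful, and the Aim 3 model cannot address it.
- Sensitivity models are commonly left to an analysis plan, which is not shown. This has force, and rules out calling the point an error. However, the covariate list is stated explicitly and applied to every Aim 3 outcome.
- The size depends on SDs and effect strengths that no section gives. This also stands. At r = 0.2 the rates are modest, and at the low end barely above 5%.

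A reader might also infer that a non-significant DLMO term would settle the matter in favour of alignment. It would not: at r = 0.2 the check misses more than half of pure timing effects.

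**Conclusion.** The point holds as a gap in interpretation that is cheap to close. Given the definition of alignment and the listed covariates, an onset-only or DLMO-only effect on 12-month change could be read as an alignment effect. That at least one of the two enters at half its size or more follows from the definition alone. How often this would produce a significant alignment term rests on the assumed component SDs, the duration–onset correlation and the effect strength, and on simplifying the three-visit mixed model to one change score.

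The stronger reading, that a timing effect would necessarily be reported as alignment or that the Aim 3 analysis is invalid, is not supported. The documents give no component SDs, one of the two leaks can be negligible, and the planned slope remains a valid estimate of the association with the interval as defined.

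**What to change.** Keep the stated model as primary. For each Aim 3 outcome, pre-specify one companion model that replaces alignment with baseline sleep onset time and baseline DLMO time, each interacting with visit, with the other covariates unchanged. Alignment plus DLMO is an equivalent parameterisation.

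In every case, report both component coefficients with confidence intervals, and the joint test over the two visit contrasts that they are equal and opposite. Describe a result as specific to alignment only if both estimates and their intervals are consistent with opposite effects of similar size; otherwise describe it as an association with sleep or circadian timing. Do not take a non-significant DLMO term as proof of an alignment effect. Settle this before outcome results are seen.

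The cost is one extra model per outcome on data already planned. In the companion model the alignment standard error is about 4–35% larger under these assumptions, and more under wider SDs. The primary model and its precision do not change.

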### Sample size justification

Sample size determinants: We aim to enroll 120 subjects and, accounting for a 20% attrition rate, this will allow us to collect complete data on 96 subjects. Based on standard deviations of 32.1 mg*L^2/(mmol*mU*min) or insulin sensitivity index [33] and 57 min for circadian alignment, we can estimate the minimum detectable effect at 80% power to be 0.161 mg*L^2/(mmol*mU*min) /min for a univariable linear regression. Further assuming a correlation of 0.4 between the covariates and circadian alignment, we can estimate the minimum detectable effect (of circadian alignment on insulin sensitivity index) in the multiple regression to be 0.176 mg*L^2/(mmol*mU*min). We will use all available resources to recruit the planned number of participants, but due to slowdowns and stoppages related to the COVID-19 pandemic, we may not reach the full sample size planned for this study. If we enroll 100 participants rather than 120, it will increase the minimal detectable effect size by 9.5%. If we enroll 110 participants, it will increase the minimal detectable effect size by 4.5%.

### Missing data

Our longitudinal analyses employ restricted maximum likelihood estimation which will provide approximately unbiased results in the presence of missing data so long as the pattern of missingness follows a missing at random pattern after accounting for the non-missing measurements of the variables included in the model [34]. Nonetheless, fully sequential multiple imputation will be the primary method used to address missing data [35]. The imputation models will include all variables in the respective outcome models plus additional variables identified as likely related to the risk of missingness or the values of the variables being imputed. In particular, any nonmissing baseline, 6 week or 12 week or 1-year measurements for a given outcome will be included in imputation models for that outcome. The application of multiple imputation will assure that statistical inferences are approximately unbiased so long as the mechanism of missingness follows a missing at random [MAR] structure [36] after accounting for both the analysis variables and additional auxiliary variables in the imputation models.

### Data collection and management

Data will be captured using the REDCap automated data system. Measures will be directly entered into the case report forms whenever possible. We will score and process wrist actigraphy files quarterly. [name] will visually review scoring for all files and re-score at least 10% of scored wrist actigraphy quarterly for quality control. If values are > 10% different, the study coordinator will undergo re-training.

## Discussion

This study extends results of laboratory-based experimental research to evaluate the impact of these sleep/circadian factors on adults in their daily lives. Results will advance understanding of the mechanisms by which sleep and circadian rhythms link to the neurobehavioral processes that affect eating behaviors, including impulsivity and the underlying metabolic risk factors. We will be able to examine how time of day affects the ability to delay gratification and hedonic eating behaviors and also whether sleep and circadian alignment affect change in cardiometabolic risk over 1-year period.

Strengths of this study include detailed, objective measurement of sleep and circadian timing, gold-standard methods of metabolic testing, and use of standardized neurobehavioral tests and ecologically valid tests of hedonic eating behaviors. On the other hand, limitations to this study include a highly screened sample free from depression, sleep disorders and substance abuse (which limits generalizability). The ongoing effects of the COVID-19 pandemic on enrollment and retention on research studies may affect the power to observe our hypothesized relationships, despite our best efforts to overcome these challenges.

In conclusion, this protocol will examine key neurobehavioral and metabolic processes that are hypothesized to link sleep loss and circadian rhythm misalignment to increased risk for cardiometabolic disorders. Results will advance the translation of laboratory research by increasing the understanding of how circadian rhythm misalignment and short sleep duration interact to increase risk for cardiometabolic diseases in naturalistic settings.

## Data Availability

N/A.

## Abbreviations

BMI: Body mass index
DLMO: Dim light melatonin onset
HbA1c: Glycated hemoglobin
SI: Insulin sensitivity index
AIRg: Acute insulin response to glucose
DI: Disposition index
BART: Balloon analogue risk task
ASA-24: Automated self-administered 24 h diet recall
HEI: Healthy eating index
